### Assignment of intervention

#### Sequence generation

Participants satisfying the eligibility criteria will be allocated to control and intervention groups equally (1:1) using the simple random sampling technique. The randomization assignment will be generated by one independent investigator using a computer-generated random number sequence.

#### Concealment mechanism

Sequentially numbered, opaque, sealed, color-coded envelopes will be used to conceal the allocation sequences. To assign the patient to the appropriate group, the investigator who is involved in randomization must first open the subsequent color-coded envelope (treatment or control). The treatment and control groups shall be designated as either “A” or “B” and this allocation shall be kept in a sealed envelope in a secure place during the study.

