### Sample size

A sample of 44 healthcare employees who engage in shift work will be recruited for the study after screening for eligibility against the inclusion and exclusion criteria mentioned below. The minimum sample size will be calculated based on the primary outcome, the proportion of participants achieving 5% weight loss after 8 weeks. Previous weight loss intervention trials predicted that 50% of individuals in the intervention group and 10% of participants in the control group would lose at least 5% of their baseline body weight after 8 weeks [23].. To detect this difference in the proportion of participants achieving 5% weight loss between the intervention and control groups, 17 participants were required in each group, to ensure 80% power at a 5% significance level. To accommodate a 20% dropout rate, we, therefore, needed to recruit 22 participants in each intervention group. Hence, a total of 44 adults with obesity (BMI >25 kg/m^2^) will be recruited for the study [24]. The formula used for sample size calculation is presented below:$${n}_B=\left(\frac{P_{\textrm{A}}\left(1-{P}_{\textrm{A}}\right)}{K}+{P}_{\textrm{B}}\left(1-{P}_{\textrm{B}}\right)\right){\left(\frac{Z_{1-\alpha /2}+{Z}_{1-\beta }}{P_{\textrm{A}}-{P}_{\textrm{B}}}\right)}^2$$

*n*
_B_ = Sample size in one arm

*P*
_A_ = Proportion of subjects expected to achieve 5% weight loss at the end of 8 weeks in the placebo group (0.1)

*P*
_B_ = Proportion of subjects expected to achieve 5% weight loss at the end of 8 weeks in the treatment group (0.5)

*Κ* = Sampling ratio (1:1)

*Z*
_α_ = Critical value of the normal distribution at *α* (*α* is 0.05 and the critical value is 1.96)

*Z*
_β_ = Critical value of the normal distribution at *β* (*β* is 0.2)

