#### Implementation

After all the participants have finished the screening and baseline assessments, participants will be informed of their randomized assignment. Eligibility evaluation and enrolment will be conducted by one independent investigator, while randomization will be done by another investigator.

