#### Interventions

The test group will be provided with a 200-kcal meal replacement shake consisting of 20.0 g of protein, 4.5 g of fat, 18.2 g of carbohydrate, and 3.6 g of fiber with other vitamins and minerals. The ingredients and the nutritional composition of the product are presented in Additional file 2. The meal replacement will be donated by a pharmaceutical manufacturing company (Astron Limited). However, the manufacturer/sponsor organization will not be involved in any aspects related to the conduct of the study, including patient recruitment, follow-up, and analysis of data.

The meal replacement product will be in powdered form, and participants will be instructed to prepare the liquid shake by mixing 53 g of powdered meal replacement with 400 mL of water. They will be asked to consume one serving of the meal replacement shake to replace dinner for 5 days of the week for a period of 8 weeks. The intervention group will be given sufficient meal replacement tins with a label indicating the ingredients and the preparation method. Participants will be instructed not to consume any additional food between dinner in the evening, and breakfast the following morning. The breakfast and lunch meals will be recommended as normal meals (the meals that they habitually eat).

The control group will be asked to continue their usual dinner meals during the study period. In addition, both the groups will be given general dietary and lifestyle advice through the distribution of leaflets which includes basic dietary advice according to Sri Lankan food-based dietary guidelines. Both groups will be advised to continue their habitual physical activities.

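### As worded, the colour on the allocation envelopes stands for the arm, which contradicts their purpose of concealing the sequence

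*Protocol article*

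**What the plan says.** Four parts of the protocol article bear on this point.

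- **Concealment mechanism, envelopes.** "Sequentially numbered, opaque, sealed, color-coded envelopes will be used to conceal the allocation sequences". To assign a patient, the investigator in charge of randomization "must first open the subsequent color-coded envelope (treatment or control").
- **Concealment mechanism, labels.** "The treatment and control groups shall be designated as either “A” or “B” and this allocation shall be kept in a sealed envelope", held in a secure place while the study runs.
- **Sequence generation.** Participants "will be allocated to control and intervention groups equally (1:1) using the simple random sampling technique", from a computer-generated list produced by an independent investigator.
- **Implementation.** "After all the participants have finished the screening and baseline assessments, participants will be informed of their randomized assignment". Also: "Eligibility evaluation and enrolment will be conducted by one independent investigator, while randomization will be done by another investigator".

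The Interventions section shows that the two arms cannot be confused in use. One receives the shake, while for the other "The control group will be asked to continue their usual dinner meals during the study period".

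**The concern.** Sealed opaque envelopes work because nobody can tell the next assignment until the envelope is opened, by which time the participant is committed. A colour on the outside that stands for the arm removes that protection, since opacity and a seal hide only the card. Anyone looking at a numbered stack could then read the next assignment and all those after it.

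What is at stake is selection at the point of allocation. The primary outcome is the proportion losing 5% of body weight, which plausibly depends on motivation, and staff may be able to judge motivation. With 22 people per arm, a small number of steered allocations could matter. An intention-to-treat analysis compares the groups as they were formed, so it does not remove an imbalance introduced while they were being formed.

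**Working it through.** The protocol gives no figure for concealment, so the main check is a comparison of passages. The arithmetic only gives a sense of scale.

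**1. What the colour means.** The first sentence of Concealment mechanism applies the colour coding to the envelopes themselves. The second repeats it and adds a parenthesis naming the two arms. Nothing else in the article gives the colour another meaning, says it is unrelated to the arm, or places it inside the envelope. On the plain wording, outer colour equals arm.

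**2. Whether other provisions prevent disclosure.**

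| Provision | What it protects | What it leaves open |
|---|---|---|
| Opaque, sealed, numbered | The card inside, and the order of use | The colour outside |
| A/B labels with a sealed key | The link from label to arm | One arm gets a shake and the other does not, so the first allocations show what each colour means |
| Different people enrol and randomize | The enrolling investigator does not perform the allocation | It is not said that the enrolling investigator cannot see the stack, and the randomizing investigator handles it |
| Participants told after screening and baseline | Baseline measurements, and much of the scope for deferring enrolment | When participants are told is not what staff can see; the order in which participants meet the envelopes is not fixed |

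No row closes the gap. Together, the last two rows reduce it mainly to one route: re-ordering people who are already enrolled.

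**3. Predictability.** Under a concealed 1:1 simple random sequence, the next assignment can be guessed correctly 50% of the time. If the colour marks the arm and the person deciding the order sees the stack, this becomes 100%. Both conditions are needed.

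**4. The plan's own figures (Sample size).** The planning assumption is that "50% of individuals in the intervention group and 10% of participants in the control group would lose at least 5"% of baseline weight, a planned difference of 50 − 10 = 40 points. The stated formula gives

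(0.1 × 0.9 + 0.5 × 0.5) × ((1.96 + 0.8416)/0.4)² = 0.34 × 49.06 = 16.68, rounded up to 17 per arm.

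Allowing for 20% dropout, 17/0.8 = 21.25, rounded up to 22 per arm and 44 in total. The stated sample size reproduces, and the fix does not change it.

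**5. Illustrative size of a two-for-two swap.** Suppose two people likely to respond are moved into the shake arm in exchange for two unlikely to respond, with all 22 per arm analysed. The number two is an assumption. Let d_S and d_C be the differences in response probability between the likely and unlikely pairs on the shake and on the usual dinner. The expected shift in the risk difference is

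2·d_S/22 + 2·d_C/22.

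- **Upper bound:** d_S = d_C = 1 gives 2/22 + 2/22 = 4/22 = 18.2 points. This needs two people certain to respond and two certain not to, whichever arm they are in.
- **Milder assumption:** 70% against 30% on the shake (d_S = 0.4) and 20% against 0% on the usual dinner (d_C = 0.2) gives 0.8/22 + 0.4/22 = 1.2/22 = 5.5 points.

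The upper bound is extreme by the plan's own assumptions. At a 10% control rate, about 0.10 × 22 = 2.2 controls are expected to respond, so the swap would take nearly all of them out of the control arm.

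**The case against.** The strongest reply is that the sentence is loosely written and the parenthesis describes the contents. The envelopes are opaque and sealed, their stated purpose is concealment, and the investigator has to open one in order to assign. Opening would be pointless if the colour already gave the answer. This has force as evidence of what the authors intended. It does not change what the text specifies: a site following it literally could sort envelopes by arm and colour, and a reader cannot tell that concealment was achieved. It lowers confidence in the reading and does not remove the need to correct the sentence.

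The second reply is that the Implementation section already limits abuse, and this largely stands. A reader might infer that enrolment could be freely timed or deferred to suit the next colour. The document does not support that: enrolment and randomization are in different hands, and, read literally, everyone completes screening and baseline before assignments are disclosed. What remains is re-ordering by someone who handles or sees the stack.

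A reader might also infer that the investigators work alongside the participants and know them well. The Population and Recruitment sections establish only that participants are employees of the hospital where the trial is run.

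Finally, a reader might take 18 points as the expected bias. It is the ceiling of a hypothetical swap. Neither the number of swaps nor the response probabilities come from the protocol, and milder inputs give 5.5 points.

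**Conclusion.** Wrong as written, with moderate confidence. The section specifies envelopes whose colour, on the plain reading, shows the arm before opening, and this contradicts its stated purpose. The A/B labels do not prevent it, and the separation of roles and late disclosure limit the scope for steering without removing it.

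The documents do not support the stronger conclusion that concealment is certainly defeated. That needs two things the article does not settle: that the colour is on the outside and maps to the arm, and that someone able to influence the order of allocation sees the stack.

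The size of any bias cannot be derived from the document. For one assumed two-for-two swap with 22 analysed per arm, the shift lies between zero and 18.2 points, against a planned difference of 40.

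**What to change.** Rewrite the two envelope sentences in Concealment mechanism. Keep the sequential numbering, opacity and sealing already specified. Drop the colour coding, and state that the envelopes are identical on the outside apart from their number and that the arm appears only on the card inside. Add that each envelope is opened only after the participant's ID and completed baseline have been recorded, which fixes who receives it.

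If the colour was never meant to indicate the arm, say so and say what it does indicate.

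Central release by phone or web would also work but is optional. Separation of list generation from enrolment is already largely covered in Sequence generation and Implementation.

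The cost is a sentence or two of text and plain envelopes; sample size and analysis are unchanged. The Trial status section says that enrolment had not started, so at that point the change could still be made before the first allocation. Concealment cannot be restored for allocations already made.

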#### Implementation

After all the participants have finished the screening and baseline assessments, participants will be informed of their randomized assignment. Eligibility evaluation and enrolment will be conducted by one independent investigator, while randomization will be done by another investigator.

#### Interventions

The test group will be provided with a 200-kcal meal replacement shake consisting of 20.0 g of protein, 4.5 g of fat, 18.2 g of carbohydrate, and 3.6 g of fiber with other vitamins and minerals. The ingredients and the nutritional composition of the product are presented in Additional file 2. The meal replacement will be donated by a pharmaceutical manufacturing company (Astron Limited). However, the manufacturer/sponsor organization will not be involved in any aspects related to the conduct of the study, including patient recruitment, follow-up, and analysis of data.

The meal replacement product will be in powdered form, and participants will be instructed to prepare the liquid shake by mixing 53 g of powdered meal replacement with 400 mL of water. They will be asked to consume one serving of the meal replacement shake to replace dinner for 5 days of the week for a period of 8 weeks. The intervention group will be given sufficient meal replacement tins with a label indicating the ingredients and the preparation method. Participants will be instructed not to consume any additional food between dinner in the evening, and breakfast the following morning. The breakfast and lunch meals will be recommended as normal meals (the meals that they habitually eat).

The control group will be asked to continue their usual dinner meals during the study period. In addition, both the groups will be given general dietary and lifestyle advice through the distribution of leaflets which includes basic dietary advice according to Sri Lankan food-based dietary guidelines. Both groups will be advised to continue their habitual physical activities.

### Study groups

The treatment group will receive the meal replacement shake for their dinner. The control group will be advised to continue their routine dinner.

### Study period

The study lasts for 8 weeks, and periodic measurements will take place at screening (visit 0), 4 weeks (visit 1), and 8 weeks (visit 2) (see Fig. 1).

**Fig. 1 Fig1:**
[figure not shown]
CONSORT flow diagram

### Primary outcome

The primary outcome will be the proportion of participants that had a 5% body weight loss from baseline.

### Secondary outcomes

Changes in waist circumference, hip circumference, percentage of body fat, and fat-free massChange in systolic blood pressure and diastolic blood pressureChange in lipid profile from baseline—total cholesterol, low-density lipoprotein (LDL), high-density lipoprotein (HDL), and triglyceridesChanges in glycemic control measures from baseline—fasting blood sugar, glycated hemoglobin (HbA1c)

### Procedures

#### Recruitment

Healthcare employees of the Nawaloka Hospitals PLC, Colombo, Sri Lanka, will be recruited voluntarily for this study by advertising through notices and distribution of leaflets with study information. Screening to identify eligible participants for the trial will be done by the research team and eligible participants will be given a detailed information sheet about the trial. The consent form will declare that participants are free to leave the study at any time, for any reason, without affecting their ability to receive future care and without being required to explain their decision. Further, the participant will have as much time as they need to think over and will have the chance to talk to the principal investigator or any other person before deciding whether or not to take part in the study. Next, the potential participants will be handed the consent form (Additional file 4) and given the chance to ask questions regarding the research. The informed written consent will be obtained by the principal investigator.

#### Study schedule

Anthropometric measures, blood pressure, fasting plasma glucose, serum HbA1c, and lipid profile will be measured at the time of recruitment of participants and will be repeated at the end of the 8th week. However, anthropometry measures will be again measured at the end of the 4th week additionally. The details of items that will be measured at every visit are described in Table 1.

### Measurement tools

#### Anthropometric measurements

Anthropometric measurements will be performed using calibrated equipment by trained personnel adhering to international recommendations. Height will be taken to the nearest 0.1 cm, as the maximum distance to the uppermost position on the head from heels, with the individual standing barefoot and in full inspiration using a calibrated stadiometer (Seca 213 portable stadiometer). Body weight will be measured to the nearest 0.1 kg using a calibrated digital weighing scale (Seca 813, Hamburg, Germany) with the participants wearing indoor light clothing and emptying the bladder. Waist circumference will be measured midway between the iliac crest and the lower rib margin at the end of normal expiration using a plastic flexible tape to the nearest 0 .1 cm. Similarly, the hip circumference will be measured at the widest level over the greater trochanters level to the nearest 0 .1 cm. BMI will be calculated as body mass in kilograms divided by height in meters squared (kg/m^2^) and waist-to-hip ratio by dividing the measured waist by hip circumference.

#### Body composition

Resistance (R) and reactance (X) will be assessed by bio-electrical impedance analysis (BIA) using a commercial portable device (Bodystat 1500, Bodystat Ltd, Isle of Man, British Isles) with hand-to-foot single frequency measurement while the subject remained supine. The participants will be asked to lie in the supine position, and then the electrodes of the BIA device will be placed on the right hand and foot. Metal objects will be removed from the body, and measurements will be taken at room temperature. To calculate fat-free mass and BF%, the resistance and reactance values will be applied to an ethnic-specific prediction equation developed for Asians [25].

#### Dietary measurements

A culturally validated Food Frequency Questionnaire (FFQ) will be used to obtain the habitual intake of calories, macronutrients, and micronutrients [26]. The energy content of each food component will be calculated using standard energy values for the portion sizes. The daily energy intakes are to be calculated using Nutri-Survey Software (EBISpro) modified with Sri Lankan food composition data.

#### Physical activity

Physical activity will be evaluated using the International Physical Activity Questionnaire (IPAQ) short version [27].

#### Biochemical analysis

A venous blood sample of 10–12 mL will be collected from each participant after overnight fasting. Blood glucose, total cholesterol, triglycerides, and HDL-cholesterol will be determined using a Cobas c501 auto analyzer using an electrochemiluminescent immunoassay (ECLIA, Roche Diagnostics). LDL cholesterol will be determined using the Friedewald formula. HbA1c will be evaluated by ion-exchange high-performance liquid chromatography.

#### Clinical examination

Seated blood pressure will be recorded on two occasions after at least a 10-min rest using a digital blood pressure monitor (Omron Healthcare, Singapore).

#### Compliance calculation

Powdered meal replacement will be dispensed to each participant at baseline, end of the 2nd, 4th, and 6th weeks. Participants will be instructed to return any unused meal replacement powder to the investigator at the end of the study. Compliance will be evaluated using the following formula:$$\textrm{Compliance}\%=\frac{\left(\textrm{Distributed}\ \textrm{meal}\ \textrm{replacement}\ \textrm{quantity}-\textrm{Remaining}\ \textrm{meal}\ \textrm{replacement}\ \textrm{quantity}\right)}{\textrm{Distributed}\ \textrm{meal}\ \textrm{replacement}\ \textrm{quantity}}\times 100$$

In addition, researchers will phone participants periodically to monitor the consumption of the meal replacement. Each participant will be asked to record the meal replacement intake each day in a compliance assessment sheet provided at baseline. At each visit, these consumption records will be cross-checked with subjects. WhatsApp® groups will be created for communication with intervention and control groups.

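### The compliance formula divides by powder distributed, which is not tied to the 2,120 g prescribed, so any surplus lowers the score of a fully adherent participant and rewards extra use

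*Protocol article*

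**What the plan says.** The Compliance calculation section of the protocol article introduces the measure with "Compliance will be evaluated using the following formula" and gives:

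Compliance % = (distributed − remaining) / distributed × 100.

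On supply, the same section says "Powdered meal replacement will be dispensed to each participant at baseline, end of the 2nd, 4th, and 6th weeks". On what is left over, it says "Participants will be instructed to return any unused meal replacement powder to the investigator at the end of the study". It gives no rule for powder that does not come back. It also describes a daily intake sheet, checked with participants at visits, and periodic phone calls. None of these enters the formula.

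The Interventions section sets the regimen. Participants prepare each serving by "mixing 53 g of powdered meal replacement with 400 mL of water" and are to "consume one serving of the meal replacement shake to replace dinner for 5 days of the week for a period of 8 weeks". The quantity supplied is described only as follows: "The intervention group will be given sufficient meal replacement tins with a label indicating the ingredients and the preparation method". Neither tin size nor number of tins is stated.

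The Statistical analysis section plans both an intention-to-treat and a per-protocol analysis, and makes adherence to treatment one condition for the per-protocol set. It sets no compliance cut-off and does not cite the formula.

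**The concern.** Compliance should express how much of the prescribed treatment was taken. The formula instead expresses how much of the dispensed stock did not come back. The two agree only if the stock equals the prescription, and the protocol does not arrange for that.

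Three consequences follow:

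- A surplus lowers the score of someone who followed the regimen exactly.
- Where there is a surplus, using more than was prescribed raises the score, and since no score can exceed 100%, overuse looks like better adherence.
- The remaining quantity is known only from what participants return, once, at the end. A participant who leaves and returns nothing has no measured remainder, and entering zero would produce a perfect score.

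At stake are the compliance figure that the trial will report and any per-protocol classification that uses it. The protocol states this formula explicitly, so the point concerns a rule that is fixed badly and not a detail left for another document.

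**Working it through.** The protocol states no compliance value or threshold, so there is no figure of its own to reproduce.

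**Inputs (Interventions and Compliance calculation sections).** Serving 53 g; 5 servings a week; 8 weeks; 4 dispensings (baseline and the ends of weeks 2, 4 and 6). Quantity dispensed, D: not stated.

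**Prescribed amount.** 5 × 8 = 40 servings; 40 × 53 g = 2,120 g, or 530 g per two weeks.

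**Full adherence, all surplus returned.** Remaining = D − 2,120, so the formula gives 2,120 / D. For a surplus s, D = 2,120 × (1 + s) and the score is 100 / (1 + s):

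| Assumed supply | Protocol formula | Divided by 2,120 g |
|---|---|---|
| Exact | 100% | 100% |
| 5% surplus | 95.2% | 100% |
| 10% surplus | 90.9% | 100% |
| 25% surplus | 80.0% | 100% |
| 7-day supply (56 × 53 = 2,968 g) | 71.4% | 100% |

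For comparison, a participant given the exact supply who misses 8 of 40 servings scores 32/40 = 80%. That equals the score of a participant who misses none under a 25% surplus.

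**Tin size (assumed, because not stated).** If whole tins cover each two-week period and leftovers are ignored at the next dispensing:

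- 400 g tins: 2 × 400 × 4 = 3,200 g; score 66.2%.
- 500 g tins: 2 × 500 × 4 = 4,000 g; score 53.0%.
- 530 g tins: 2,120 g; score 100%.

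If leftovers carry over and only the 8-week total is rounded up to whole tins:

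- 400 g tins: 6 × 400 = 2,400 g; score 88.3%.
- 500 g tins: 5 × 500 = 2,500 g; score 84.8%.
- 1,000 g tins: 3 × 1,000 = 3,000 g; score 70.7%.

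The shortfall therefore runs from 0 to 47 points over these cases, and the document does not locate it within that range.

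**Use beyond the regimen, 7-day supply assumed (2,968 g).**

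- 5 days a week: 2,120 / 2,968 = 71.4%.
- 6 days a week: 48 × 53 = 2,544 g; 2,544 / 2,968 = 85.7%.
- 7 days a week: 100%.

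Divided by 2,120 g, the same three patterns give 100%, 120% and 140%, so overuse becomes visible.

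**Early stop, nothing returned, read as zero remaining (assumption).** (D − 0) / D = 100% for any D, even if 1 of 40 servings (2.5%) was eaten. Dividing by 40 prescribed servings, with 10 servings per dispensing assumed, gives 25%, 50%, 75% and 100% after 1, 2, 3 and 4 dispensings. The new denominator reduces this error but does not remove it: after the fourth dispensing the score is again 100%. A rule for unreturned powder is needed as well.

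**The case against.** The strongest reply is that no shortfall can be demonstrated from the document. Tin size and number are not given, and at exact supply the formula is correct. That stands, and it limits the claim to what happens if there is a surplus. A reader might infer from tin rounding that perfect adherence will score roughly 53–71%. The document does not support that. Such figures need particular tin sizes and no carry-over of leftovers, and other equally plausible assumptions give 85–100%.

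A reader might also infer that the protocol counts unreturned powder as eaten, so that dropouts score 100%. It does not say so. It asks for unused powder back and is silent on what happens when none arrives. Nor does the denominator alone cause this problem, as the last step of the working shows.

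A third tempting inference is that the formula would keep dropouts in the per-protocol set and bias that analysis. Per-protocol membership also requires that the measurements be available, so someone who left at week 3 without a week-8 weight would be excluded whatever the powder score. Neither the per-protocol definition nor the low-compliance reason listed among the discontinuation criteria refers to the formula or to a cut-off. No per-protocol bias has been shown.

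Finally, the daily sheet, visit checks and calls give other evidence on adherence, and the sheet could record use beyond 5 days. These soften the practical effect, but they do not repair the one measure that the protocol defines numerically.

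**Conclusion.** The point holds in a limited form. The denominator is powder distributed, the protocol does not tie this to the prescribed 2,120 g, and the score is therefore not a measure of adherence to the regimen unless supply happens to be exact. Conditional on a surplus, full adherence scores 95.2% at 5%, 90.9% at 10% and 71.4% with a 7-day supply, and extra use scores higher than following the protocol. The actual size is unknown because the quantity dispensed is not stated. The 100% score for an early leaver depends further on reading a missing return as zero remaining.

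The effect is confined to the reported compliance and to any use of it for the per-protocol set. The intention-to-treat analysis of the primary outcome keeps everyone in the randomised group whatever they consumed, so it is untouched. This is a small, worthwhile correction, not a threat to the main result.

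**What to change.** Replace the formula with:

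Compliance % = (distributed − returned) / prescribed × 100,

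where prescribed is 2,120 g, or the amount due up to the date on which treatment or follow-up ended. The first describes adherence to the whole course and the second adherence up to that date, so state in advance which one is reported and which, if either, informs the per-protocol set. Do not cap the result at 100%.

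State that powder not returned is missing and not zero, and that for those participants compliance is taken from the daily intake sheet.

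The cost is a trivial recalculation using data already planned, and the Trial status section says that enrolment has not begun. Weighing leftovers at existing contacts would improve the count but is optional. Table 1 shows post-baseline visits only at weeks 4 and 8, and the protocol does not say how powder is handed over at weeks 2 and 6, so weighing at those times might need extra arrangements.
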